## Randomization Criteria

Subjects will be randomized to the study providing they fulfill all of the entry criteria at screening. A computer-generated pseudo-random code will be used to assign subjects to treatment. For the groups there will be 2 randomization lists; one for diabetic patients and one for non-diabetic patients. This is to ensure an even distribution of diabetic and non diabetic patients in the placebo group and the pregabalin group. Individual treatment codes in sealed envelopes, indicating the treatment randomization for each randomized patient, will be available to the investigator(s) at the study centre. The individual treatment codes must not be broken except in medical emergencies when the appropriate management of the patient necessitates knowledge of the treatment randomization.

# STUDY TREATMENTS

Patients will take either placebo or pregabalin, 75mg BID for the first 3 days, 150 mg BID for the next 4 days followed by 300 mg BID from Day 8 to Day 21 +14 days. If a patient does not tolerate 300mg BID it will be acceptable for them to maintain 150mg BID for the remainder of the study, following discussion and guidance from the investigator.

Pregabalin and placebo will be presented as grey capsules, which should be taken with approximately 250 ml water.

In order to maintain the blind, all patients will take doses of drug or placebo twice a day. Doses should be taken between 07:00 and 10:00 and between 19:00 and 22:00 (i.e. at approximately 12 hourly intervals).

After the last day of the study, the patients will taper their medication as detailed below:

Taper medication will be dispensed together with all other study medication at Visit 2. Taper will be administered to subjects who discontinue the study early only if they have completed 4 or more days of study drug. Thus patients who are unable to escalate from 75mg BID will simply cease medication. For all other subjects, the tapering period is 7 days.

- Subjects who were taking 300 mg BID pregabalin will have their dose reduced to 150 mg BID.
- Subjects who were taking 150 mg BID pregabalin will receive 75 mg BID.

Subjects who were taking placebo will continue on matching placebo for 7 days.

The amount of investigational products that is dispensed and returned will be recorded in the patient specific Case Report Form (CRF) by the investigator(s). It is essential that designated study personnel account for all medication. All discrepancies between amounts of investigational products dispensed and returned must be recorded and explained.

## Drug Supplies

Supplies will be provided in bottles by Pfizer Clinical Research Operations.

- Pregabalin capsules orally 75 mg (total dose of 150 mg/day)
- Pregabalin capsules orally 150 mg (total dose of 300 mg/day and 600mg/day)
- Matching placebo capsules orally.

The study drugs will be packed and labeled under the responsibility of Pfizer Clinical Research Operations.

## Concomitant Medication(s)

Patients will be instructed not to change their regular pain treatment during the trial period, this will be recorded twice, at the screening visit and the last visit. Additional pain medication (taken as needed) will be used and recorded at the telephone interviews and in the diary.

# STUDY PROCEDURES

The pain intensity, neuropathic pain component, global well-being and quality of life are tested with standardized questionnaires. The study will take place in Radboud University Nijmegen Medical Centre.

## Screening

Visit 1; Screening (28 – 7 days before the first dose of study drug):

- Obtain informed consent.
- Physical examination.
- General and specific medical history (including drug/alcohol/tobacco consumption).
- Concomitant medication.
- Questionnaires (QOLQ, mBPI-sf, PD-Q and PGIC) are filled out.
- Blood and urine for hematology, clinical chemistry and urinalysis.
- Pregnancy test (urine) will be done in females not postmenopausal for more than 1 year or not sterile.
- 12-lead ECG.
- Blood pressure and pulse rate (supine and standing). Supine BP/PR should be measured following resting for 5 minutes. Standing BP/PR should be measured following standing for 2 minutes.
- Diary instruction. The patient will start completing the pain diary 7 days prior to the first dose of study drug.
- Experimental testing (training): pressure and electrical stimulation (skin and muscle) as described below.
- Cold pressor test (training) as described below.

Patients fulfilling inclusion and exclusion criteria are randomized and invited to join the study.

The duration time of the first visit will be approximately 4 hours.

## Study Period

Seven days prior to the first dose of study drug, the patients will start to score pain levels in a pain diary. The average pain over the previous 24 hours and the worst pain over the previous 24 hours will be assessed using the VAS score. Usage of pain medication will also be recorded in the diary

Visit 2:

Day 1, first dose of study drug:

The patients visit the clinic and are instructed to start the trial medication if laboratory tests are normal. Ahead of the first dose of study drug the patients will undergo multimodal testing. They will have the skin in segments C5, T4, T10, L1 and L4 stimulated electrically. Also deep muscle pain will be assessed on the same places, using pressure stimulation. A cold pressor test is performed on the right hand and the deep muscle pain is measured on the left thigh both before and after the cold pressor test. Pain thresholds will be assessed using visual analogue scales (VAS).

These assessments are done before starting the treatment on Day 1 and on Day 21 + 14 days.

Patients will start the trial medication and score pain levels in the diary with a VAS value for the average pain over the previous 24 hours and a second VAS value for the worst pain over the previous 24 hours. Use of as needs pain medication will also be recorded in the diary.

The duration time of the second visit will be approximately 2 hours.

Telephone interviews

On days 4, 7, 11, 14 and 17 a study nurse or doctor will call the patients to assess the severity and tolerability of any adverse events.

On Day 7 a study nurse or doctor will call the patients to assess the adverse events and to administer the PD-Q and PGIC questionnaires. The dose of study drug will be discussed. Patients with acceptable adverse events will increase the dose to 300 mg BID. Patients experiencing unacceptable adverse events on 150 mg BID will be taken out of the study and will be replaced.

Visit 2:

All patients will visit the centre on day 21 + 14 days.

- Physical examination.
- Concomitant medication
- Questionnaires (QOLQ, mBPI-sf, PD-Q and PGIC) are filled out.
- Blood and urine for haematology, clinical chemistry and urinalysis.
- Pregnancy test (urine) will be done in females not postmenopausal for more than 1 year or not sterile.
- Experimental testing as described in visit 1: pressure and electrical stimulation (skin and muscle).
- Cold pressor test.

Patients will be instructed to taper their study medication by halving their study drug dose for 7 days and then stopping the medication.

The duration time of the third visit will be approximately 3 hours.

## Subject Withdrawal

If unacceptable adverse effects are experienced by the patient between the telephone calls, the patient should contact the investigator. Based on a medical judgment, the dose of study drug may be reduced and the treatment continued or the patient may be withdrawn from the study. Follow up consultations and eventually additional blood tests will be arranged as by request judged by the investigator. The minimum end dose will be 150 mg BID, otherwise the subject will be withdrawn. Withdrawn patients or dropouts will be replaced until a number of 60 patients have fulfilled the study.

# ASSESSMENTS

## Visual Analogue Scale (VAS)

Only one scale will be used in both the clinical and experimental studies to secure comprehensible and uniform recordings. A scale that has previously been shown to be reliable and robust to discriminate sensations in somatic and visceral pain will be used (Drewes *et al.* 2003c [26]). This VAS will be used to assess both non-painful and painful sensations in the skin and muscle.

It is presented as a 10-cm line, anchored by verbal descriptors: The intensity of the *non-painful sensations* will be scored with the following descriptors added to facilitate the scoring: 1 – vague perception of mild sensation; 2 – definite perception of mild sensation; vague perception of moderate sensation; 4 – definite perception of moderate perception. For the *painful sensations* the patients will use the scale from 5 to 10 anchored at 5 – pain detection threshold (denoted PDT); 6 – slight pain; 7 – moderate pain threshold (denoted MPT); 8 – medium pain intensity; 9 – intense pain and 10 – unbearable pain. This part of the scale is colored red for a clear visual separation of the non-painful and painful range of sensations.

The score is measured from the zero-anchor to the patient’s mark. Using a millimeter scale to measure the patient's score will provide 101 levels of pain intensity.

This VAS scale will also form the pain assessment in the patient diary.

## Skin and muscle stimulation

### Tetanic electrical skin stimulation

Thresholds to electrical constant current skin stimulation (Digistim; Biometer A/S, Copenhagen, Denmark; tetanic stimulation at 100Hz, 0.2ms square waves, self-adhesive electrodes 3cm apart) will be measured at the following left-sided sites: thorax (T4 dermatome), pancreatic site (dorsal T10 dermatome), arm (C5 dermatome), hip (L1 dermatome) and knee (L4 dermatome). Three thresholds will be measured: sensation (stimulation just felt, VAS = 1), pain detection (PDT, pricking pain just felt, VAS = 5) and pain tolerance threshold (PTT, burning pain, VAS = 7). These quantitative sensory testing (QST) techniques in relation to pancreatitis have been described in detail previously (Buscher *et al*., 2006 [28]).

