## Endpoints

### Primary Endpoints

The primary endpoint for the study is analgesic effect of pregabalin therapy.

In the *clinical part* of the study, the primary efficacy parameter for analgesic effect is pain relief. This is defined as the reduction in VAS pain scores at the end of the study (day 21) as compared to the pre-treatment level. This effect is further assessed as changes in the daily experience of pain, which will be assessed using questionnaires, including the modified brief pain inventory-short form (mBPI-sf), the pain*DETECT* questionnaire (PD-Q, Freynhagen *et al*. 2006 [21]) and patient global impression of change (PGIC, Farrar *et al*. 2001 [22]).

In the *experimental part*, the primary endpoint for analgesic effect is change in pain processing. This is defined as the reduction pain tolerance thresholds in the dermatomes at the end of the study (day 21) as compared to the pre-treatment level. Pain processing will be assessed using QST parameters. All changes are compared to baseline recordings.

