### Deep muscle stimulation

The pressure pain tolerance threshold (PPTT) will be determined on the quadriceps muscle and on the same localizations as the tetanic electrical skin stimulation by pressing an electronic pressure algometer (Somedic AB, Stockholm, Sweden) on the muscle group. The probe has a surface area of 1cm2. The pressure will be increased at a rate of 30 kPa/sec until the PTT (VAS = 7) is reached.

The patients will be instructed to press a button when PTT is reached.

PPTT is determined to be the average of 2-3 consecutive assessments separated by two-minute intervals.

The assessment parameter will be mean value of PPTT in kPa.

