## Cold pressor test in combination with pressure stimulation

In this combined test, the patient will rate the pain evoked by pressure both before and immediately after application of the cold pressor test.

The test will therefore consist of three parts (the details of the cold pressor test are outlined below:

1. PPTT determination as described above on the left quadriceps muscle.
2. Cold Pressor test on the right hand
3. Repetition of the PPTT determination on the left quadriceps muscle.

Cold pressor test: The right hand is immersed in ice-chilled water (1.0°C ± 0.3°C) that is continuously stirred by a pump. The patient will be told to remove the hand from the water after 2 minutes of immersion - or sooner if the pain is considered to be intolerable. The patients continuously rate the pain intensity during the cold pressor test with the use of an electronic visual analogue scale coupled to a computer with software designed for this purpose. From the data obtained, the peak-pain intensity (VASpeak), and the average area under the pain intensity-time curve (VASAUC), will be determined (Jones et al., 1988 [30]). Immediately after the cold pressor test, the patients will rate the discomfort experienced during the test by use of a visual analogue scale. If the patient withdraws their hand sooner than two minutes, due to intolerable pain, the VAS will be considered to be 10 for the remaining time.

The assessment parameters will be VASAUC (for 2 min or shorter duration), VASpeak (during the 2 min) (in mm) and time to reach “intolerable pain”, for example before reaching the 2 min goal (in sec).

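### The experimental primary endpoint is called pain tolerance threshold but is measured at VAS = 7, which the protocol's own scale defines as the moderate pain threshold

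*Protocol*

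**What the plan says.** Protocol Section 2.2.1 defines the primary endpoint of the experimental part as the "reduction pain tolerance thresholds in the dermatomes at the end of the study (day 21", relative to the pre-treatment level.

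The measurement rules are in Section 7.2. For electrical skin stimulation (7.2.1) the third of three thresholds is the "pain tolerance threshold (PTT, burning pain, VAS = 7". For pressure on muscle (7.2.2): "The pressure will be increased at a rate of 30 kPa/sec until the PTT (VAS = 7) is reached". The patient then presses a button when PTT is reached.

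Section 7.1 describes the scale on which these numbers are read: "Only one scale will be used in both the clinical and experimental studies to secure comprehensible and uniform recordings". Its upper anchors are "7 – moderate pain threshold (denoted MPT); 8 – medium pain intensity; 9 – intense pain and 10 – unbearable pain".

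In the cold pressor test (7.3), if the hand is withdrawn early "due to intolerable pain, the VAS will be considered to be 10 for the remaining time".

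Section 2.2.2 adds that baseline recordings will be compared with published normal values from healthy controls.

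**The concern.** One scale point carries two names that mean different things. As tolerance, it is the most the patient will accept. As the moderate pain threshold, it is a level with three stronger anchors above it. The measurement belongs to a primary endpoint, so the name decides what the trial may conclude.

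Two things are at stake. First, an effect on the stimulus that evokes moderate pain would be reported as an effect on tolerance. Second, a patient or operator who follows the word may stop at a higher stimulus than one who follows the number. No analysis plan can repair that afterwards, because the data record only the stimulus at which the test stopped, not the rule behind it.

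**Working it through.** No figure in the plan depends on this point, so the check sets the definitions side by side.

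| Scale point | Meaning in Section 7.1 | Use in Sections 7.2 and 7.3 | Agree? |
|---|---|---|---|
| 1 | first, vague sensation | sensation threshold (7.2.1) | yes |
| 5 | pain detection threshold, PDT | pain detection, PDT (7.2.1) | yes |
| 7 | moderate pain threshold, MPT | pain tolerance threshold, PTT (7.2.1, 7.2.2) | **no** |
| 8 | medium pain | none | – |
| 9 | intense pain | none | – |
| 10 | unbearable pain | intolerable pain, cold pressor test (7.3) | yes |

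1. *Is Section 7.2.1 using a different scale?* No. Section 7.1 says there is only one, and the other two thresholds in 7.2.1 match it. Only the threshold that carries the primary endpoint departs. The abbreviation MPT is introduced in 7.1 and never used again.

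2. *Where does 7 lie?* The painful range runs from 5 to 10, so 7 is (7 − 5)/(10 − 5) = 2/5, or 40%, of the way along it. This is a position on the rating scale. It says nothing about how much weaker the stimulus is.

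3. *What does the trial estimate if 7 is applied uniformly?* Write S7 for the stimulus at which a patient reports 7. Each patient's change is S7(end) − S7(baseline), and the difference between arms estimates the treatment effect on S7. Randomisation protects that comparison whatever S7 is called. It is not an estimate of the effect on the tolerated stimulus unless the drug shifts both alike, which the protocol neither states nor measures.

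4. *What if it is not applied uniformly?* The protocol does not give the words spoken to the patient. Section 7.2.1 offers a name (tolerance), a quality (burning) and a number (7). Section 7.2.2 ties the button to PTT. Section 3 plans 30 patients in each of two countries, and Section 4.3 splits the randomisation lists by diabetes only. Different readings between patients or centres would mix two quantities. In a double-blind trial the reading chosen should be unrelated to treatment, so the expected result is added variance.

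5. *Can the noise be sized?* No. The protocol gives neither a stimulus-response relation nor a standard deviation for the threshold. The sample size in Section 9.1.2 rests on pain VAS (a 2 cm decrease, SD 2.4 cm), not on this endpoint.

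**The case against.** The strongest reply is that PTT is a defined term. Sections 7.2.1 and 7.2.2 both give VAS = 7, so a careful reader knows what was measured and the label is secondary. The button sentence directly follows the one that states VAS = 7. It appears only for muscle pressure, whereas the primary endpoint refers to dermatomes, which are named for the electrical test (although pressure is applied at the same locations). Section 6.1 schedules training in both kinds of stimulation before baseline. The rule in Section 7.3 is a scoring convention for another test and does not define PTT.

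Most of this stands. The number is explicit and consistent, training makes divergent stopping less likely, and Section 7.3 is supporting evidence only. But Section 7.1 defines 7 without any help from Section 7.3, and Section 2.2.1 names the endpoint by the word with no scale point. A defined term that contradicts the scale it is defined on does not license a conclusion in the ordinary sense of that term.

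A reader might go further and infer that patients will look falsely hyperalgesic beside healthy controls. The documents do not support this. They do not say which normal values will be used or how those were obtained, and the definition in the pilot study cited for the technique cannot be checked here. The norms may have been taken at the same point.

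**Conclusion.** The contradiction is real and lies in the operational definition of a primary endpoint. Its consequence is limited. With VAS = 7 applied uniformly, the treatment comparison is valid but misnamed: it supports a statement on the moderate pain threshold, not on tolerance. The ambiguity also carries an avoidable risk of uneven stopping, which would add noise of unknown size.

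Two stronger readings should be resisted. One is that the randomised comparison is biased. Nothing in the protocol suggests that the stopping rule would differ by arm. The other is that a percentage can be put on the shift in stimulus, or on a spurious change between visits. That would need an assumed relation between stimulus and rating, and a patient who switches fully from one definition to the other. The protocol gives no basis for either.

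The verdict assumes that the scale in Section 7.1 governs the tests in Section 7.2, as Section 7.1 itself says. The point is worth correcting because the change is cheap and settles what may be concluded.

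**What to change.** Keep the measurement at VAS = 7 and bring the text into line with the scale:

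- In Sections 2.2.1, 7.2.1 and 7.2.2, name the endpoint moderate pain threshold (stimulus at VAS = 7). The pressure abbreviation carried into Section 7.3 should follow.
- For both the skin and the muscle test, state the patient's cue as the moment the sensation reaches 7 on the scale, and use the same words at every centre and visit.
- Word the experimental conclusions as effects on the moderate pain threshold.
- For the comparison in Section 2.2.2, use published normal values obtained at the same scale point, or state the difference in definition beside the result.

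The cost is protocol wording and one line of test instruction, with no extra procedure, visit or patient. The small downside is that the result can no longer be called pain tolerance.

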### Deep muscle stimulation

The pressure pain tolerance threshold (PPTT) will be determined on the quadriceps muscle and on the same localizations as the tetanic electrical skin stimulation by pressing an electronic pressure algometer (Somedic AB, Stockholm, Sweden) on the muscle group. The probe has a surface area of 1cm2. The pressure will be increased at a rate of 30 kPa/sec until the PTT (VAS = 7) is reached.

The patients will be instructed to press a button when PTT is reached.

PPTT is determined to be the average of 2-3 consecutive assessments separated by two-minute intervals.

The assessment parameter will be mean value of PPTT in kPa.

## Cold pressor test in combination with pressure stimulation

In this combined test, the patient will rate the pain evoked by pressure both before and immediately after application of the cold pressor test.

The test will therefore consist of three parts (the details of the cold pressor test are outlined below:

1. PPTT determination as described above on the left quadriceps muscle.
2. Cold Pressor test on the right hand
3. Repetition of the PPTT determination on the left quadriceps muscle.

Cold pressor test: The right hand is immersed in ice-chilled water (1.0°C ± 0.3°C) that is continuously stirred by a pump. The patient will be told to remove the hand from the water after 2 minutes of immersion - or sooner if the pain is considered to be intolerable. The patients continuously rate the pain intensity during the cold pressor test with the use of an electronic visual analogue scale coupled to a computer with software designed for this purpose. From the data obtained, the peak-pain intensity (VASpeak), and the average area under the pain intensity-time curve (VASAUC), will be determined (Jones et al., 1988 [30]). Immediately after the cold pressor test, the patients will rate the discomfort experienced during the test by use of a visual analogue scale. If the patient withdraws their hand sooner than two minutes, due to intolerable pain, the VAS will be considered to be 10 for the remaining time.

The assessment parameters will be VASAUC (for 2 min or shorter duration), VASpeak (during the 2 min) (in mm) and time to reach “intolerable pain”, for example before reaching the 2 min goal (in sec).

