### Secondary Endpoints

Secondary efficacy parameters are changes in quality of life compared to baseline level. The European Organization for research and treatment of cancer quality of life questionnaire (QOLQ, Bloechle *et al.* 1995 [23], will be used. Also the tolerability of the drug in this patient population will be compared to placebo.

In the experimental part of the study the difference of the QST stimulus are considered secondary efficacy parameters. The experimental baseline recordings will also be compared to published normal values from healthy controls to evaluate general aspects of pain processing in the patient group.

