### Analysis of Secondary Endpoints

Changes in the secondary endpoints will be analyzed with a non-parametrical test (Mann-Whitney U) Effect of the active treatment is evaluated and presented with 95% confidence intervals.

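### Cold pressor time to intolerable pain is cut off at 120 s, yet on the natural reading it is analysed as a change from baseline, which dilutes the effect and loses power on this one secondary parameter

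*Protocol*

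**What the plan says.** Protocol Section 7.3 fixes the length of the test: "The patient will be told to remove the hand from the water after 2 minutes of immersion", or sooner if the pain is intolerable. It names three parameters. Two are VAS measures: "The assessment parameters will be VASAUC (for 2 min or shorter duration), VASpeak (during the 2 min) (in mm"). The third is the time: "time to reach “intolerable pain”, for example before reaching the 2 min goal (in sec").

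For the VAS measures there is a rule after early withdrawal: "If the patient withdraws their hand sooner than two minutes, due to intolerable pain, the VAS will be considered to be 10 for the remaining" part of the test. There is no matching rule for the time of a patient who keeps the hand in for the full 2 minutes.

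Section 2.2.1 says of the experimental part: "All changes are compared to baseline recordings". Section 2.2.2 sets the tier: "In the experimental part of the study the difference of the QST stimulus are considered secondary efficacy parameters". The Analysis of Secondary Endpoints in Section 9 sets the quantity and the test: "Changes in the secondary endpoints will be analyzed with a non-parametrical test (Mann-Whitney U"), with 95% confidence intervals. Section 6.2 places the two measurements on Day 1 before the first dose and at the end-of-treatment visit.

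**The concern.** A patient who lasts 2 minutes has no observed time to intolerable pain. All that is known is that it exceeds 120 s, so the time is right-censored at one fixed point for everyone. Analgesia lengthens this time and so moves patients towards the cut-off.

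The trouble comes from subtracting a baseline that may itself sit at the cut-off. A patient at 120 s on Day 1 can only score zero or worse, whatever the drug does, and ranks below a patient who goes from 60 s to 70 s. The patients most tolerant at baseline are thus ranked as if they had no benefit. What is at stake is a weaker test and an effect estimate pulled towards zero for one of the three cold pressor parameters.

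**Working it through.** **No stated figure to reproduce.** The protocol gives no expected time, spread, effect or completion rate for this parameter.

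**Inputs from the protocol.** The cut-off is 120 s (Section 7.3). The experimental part has 60 patients (Section 9.1.2), and Sections 4 and 6.3 also ask for 60 completers. With equal arms (assumed), that is 60/2 = 30 per arm. The planned analysis is Mann-Whitney U on the change.

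**Assumed inputs.** Times are log-normal with log-SD 0.8 and a between-visit correlation of 0.7. The drug multiplies time by exp(0.5) = 1.65. The share lasting 2 minutes at baseline is 10%, 25%, 40% or 60%. The test is two-sided at 5%.

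**Effect of the cap on one patient.** Recorded change = min(end, 120) − min(baseline, 120). If the drug multiplies time by 1.65 and nothing else changes:
- Baseline 60 s: end 60 × 1.65 = 99 s, change 39 s, fully seen.
- Baseline 90 s: end 90 × 1.65 = 148.5 s, recorded as 120 s. The change is 30 s instead of 58.5 s.
- Baseline 120 s or more: change 0.

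Truncation starts at a baseline of 120/1.65 ≈ 73 s.

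**Power by simulation, 30 per arm, true ratio 1.65.** Mann-Whitney on the change has power of about 0.84 with no cap.

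| Baseline completion | Mann-Whitney on capped change | Loss against 0.84 | Rank ANCOVA of capped end time on capped baseline | Gain over planned test |
| --- | --- | --- | --- | --- |
| 10% | 0.79 | 0.05 | 0.86 | 0.07 |
| 25% | 0.70 | 0.14 | 0.84 | 0.14 |
| 40% | 0.55 | 0.29 | 0.75 | 0.20 |
| 60% | 0.38 | 0.46 | 0.59 | 0.21 |

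**Dilution of the estimate.** With the same distribution, the geometric mean ratio computed from capped times is 1.51, 1.38, 1.27 and 1.15 at the four completion rates, against the true 1.65.

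**Second set of assumptions** (30 per arm, log-SD 0.9, baseline capping 5%, 20%, 40% and 60%):
- True ratio 2.0: the planned test has power 94%, 88%, 69% and 49%, against about 95–97% uncapped. Rank ANCOVA has 97%, 95%, 88% and 75%.
- True ratio 1.5: the planned test has 54%, 47%, 36% and 28%, against about 54–57% uncapped. Rank ANCOVA has 61%, 55%, 48% and 38%.
- Hodges-Lehmann difference at ratio 2.0: it falls from 27 to 23 s, 55 to 25 s, 95 to 16 s and 147 to 4 s.

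**Type I error.** With no treatment effect (second set), Mann-Whitney on the capped change rejects in 4.4% to 5.4% of runs. Rank ANCOVA rejects in 4.8% to 5.1%.

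**The case against.** The route to Mann-Whitney on the change is an inference. Cold pressor time is never named as a secondary endpoint, and Section 2.2.1 also mentions QST parameters under the primary endpoint, which is analysed by ANCOVA. This stands as a caveat. The secondary reading remains the natural one, because the experimental primary endpoint is defined by tolerance thresholds in the dermatomes. How completers are scored is also commonly left to a statistical analysis plan, which is not shown, so the missing scoring rule is not a fault by itself. The change score, however, is fixed in the protocol.

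Stronger readings are tempting, but the document does not support them:
- A reader might infer that anyone who lasts 2 minutes cannot show analgesia. Only baseline completers are blocked, and only on this parameter. A patient who moves from 60 s to 120 s shows a gain of 60 s. VASAUC and VASpeak can still fall in completers, and VASAUC partly reflects tolerance time through the rule that sets VAS to 10.
- A reader might infer that completers would be left out as having no event. The protocol says this nowhere.
- A reader might blame the Mann-Whitney test. With one common cut-off, censored end times can be ranked as ties at the top. The fault lies in ranking differences from a capped baseline.
- A reader might attribute the whole gap between the planned test and a baseline-adjusted model to censoring. With 24 per arm and no cap at all, Mann-Whitney on the change has power of about 0.75 and a log-scale ANCOVA 0.83. That part of the gap comes from covariate adjustment.
- A reader might infer that baseline adjustment does not help. The table shows that it makes up much of the lost power.

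Finally, the completion rate in stirred water at about 1 °C cannot be judged from this document, and at 10% the censoring loss is only about 5 points.

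**Conclusion.** The point holds in this limited form and is minor. Analysing the change from a baseline cut off at 120 s dilutes the effect on time to intolerable pain and loses power: about 5 points at 10% baseline completion, 14 at 25%, 29 at 40% and 46 at 60%. These figures rest on 30 per arm, log-normal times with log-SD 0.8 and correlation 0.7, and a true ratio of 1.65. The direction is the same under the second set of assumptions. The size depends on a completion rate that the protocol does not give: small near 10%, large from about 25%. The error is conservative: type I error is intact, and no primary endpoint depends on this parameter.

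**What to change.** In Section 7.3, state that a patient who keeps the hand in for 2 minutes is recorded as 120 s, flagged as censored, and that no such patient is dropped.

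In the Analysis of Secondary Endpoints, exempt this parameter from the change-score test. Compare end-of-treatment time between arms by rank ANCOVA on baseline time, with completers tied at the top rank. For the effect size, fit a log-normal censored (Tobit) regression that includes baseline time, and report a time ratio with 95% CI.

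The rank ANCOVA should carry the test. In 400 null runs each, with 24 per arm, the Tobit model rejected in 4.5% (25% completion) and 6.8% (40% completion). The simulation standard error at 5% is √(0.05 × 0.95/400) ≈ 1.1 points, so mild inflation is neither shown nor excluded.

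The cost is a sentence or two in each of the two places, with no new data, procedures or patients. The downsides are a slightly less simple analysis for one parameter and a time ratio that depends on a model. At high completion the fix recovers only part of the loss (0.59 at 60%).
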